#### Feasibility

Feasibility of the intervention and protocol will be evaluated through the semistructured interviews with women in cohort 1. To ascertain feasibility, open-ended questions will be asked to evaluate fidelity and resource requirements. Fidelity will be assessed by examining the five core components of the intervention with global open-ended questions for each, such as:

What have you learned about the brain (and the brain during pregnancy)?What have you learned about the nature of trauma and its effect on the brain?What have you learned about the effects trauma can have on your attachment with your baby?What have you learned about triggers?What tools have you learned about to manage triggers?

Resource requirements will be assessed from: 1) a provider perspective by tracking the length of the CBT sessions and the number of sessions; 2) a patient perspective by tracking any costs incurred to participate in the CBT session (eg, travel, childcare, etc); and 3) a system perspective by tracking the use of facilities and referrals to other resources.

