### Data Collection

Data collection will occur simultaneously for both cohorts.

#### Cohort 1

Data collection will occur at baseline (T1; prior to the PCNS-delivered CBT and during pregnancy), two (T2), six (T3), and twelve (T4) months postpartum. At T1 and T2, a mixed-method data collection model will be utilized wherein women will complete a semistructured interview for approximately one hour (audio-recorded) and complete a short demographic survey. At T3 and T4, participants will be sent an electronic link to complete a questionnaire (or alternatively, if this is thought to be unsafe, a member of the research team will meet with the participant to complete a hardcopy version).

During the T1 data collection interaction, the study protocol will be thoroughly described and consent to participate will be obtained. Throughout the data collection period (T1-T4), a detailed safety plan will be reviewed (updated as needed), and participants will be provided a $25 honorarium (retail gift card) in recognition of their contribution to the study. To further reduce potential barriers to involvement, those in need of reimbursement for childcare or transportation expenses to attend the in-person interviews will be offered $15 and $10, respectively.

#### Cohort 2

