A data abstraction instrument (developed by the co-principal investigators) will be used to collect data. Data will be pulled from multiple sources including: the e-chart, nursing chart, paper chart, and nursing care plan. Maternal data extraction will include: a) scope of mental illness, including diagnosis and current treatments; b) general physical and mental health status; c) obstetrical history; d) birth summary; e) care plan, including CBT interventions; f) evidence of learned CBT strategies or alternative coping strategies used during birth; g) birth experience; h) evidence of maternal-infant attachment; and i) demographics. Conversely, data extraction for infants at the time of parturition will include: a) gestational age; b) weight; c) length; d) head circumference; e) complications and interventions; f) Appearance, Pulse, Grimace, Activity, and Respiration (Apgar) score; and g) newborn physical exam. The chart review will take place at the recruiting hospital and does not require any patient contact. No identifying information will be collected, as the audit will be conducted for each chart in its entirety during a single data extraction period, thereby eliminating the need to refer back to any particular patient’s chart.

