## Results

The work reported here is in the proposal phase. Once the protocol is implemented, we will report the results in a follow-up paper. However, we hypothesis that PCNS-delivered CBT will result in decreased PTSD, anxiety, and/or depression symptomatology, and improved maternal-infant attachment, coping, and QOL. We also hypothesize this study will be feasible in terms of fidelity and deliverability, as well as be highly acceptable to participants.

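### Fidelity is assessed only by asking women what they learned, which measures receipt or comprehension and not whether the content was delivered as designed

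*Protocol article*

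**What the plan says.** The Feasibility section names its data source: "Feasibility of the intervention and protocol will be evaluated through the semistructured interviews with women in cohort 1". It then sets out the fidelity method: "Fidelity will be assessed by examining the five core components of the intervention with global open-ended questions for each". Five questions follow, on the brain in pregnancy, trauma and the brain, trauma and attachment, triggers, and ways of managing triggers. All ask what the woman has learned; the last reads "What tools have you learned about to manage triggers".

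The same section tracks the number and length of CBT sessions, but under resource requirements from the provider's side. The article describes no recording of sessions, no rating of them, no component checklist and no adherence criterion. The audio recording in Data Collection is of the research interview.

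Fidelity is nevertheless one of the study's hypotheses. The Results section states: "We also hypothesize this study will be feasible in terms of fidelity and deliverability". The Discussion also names fidelity as a basis for judging feasibility.

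On timing, Data Collection (Cohort 1) says: "Data collection will occur at baseline (T1; prior to the PCNS-delivered CBT and during pregnancy), two (T2), six (T3), and twelve (T4) months postpartum". Interviews belong to the first two of these: "At T1 and T2, a mixed-method data collection model will be utilized wherein women will complete a semistructured interview for approximately one hour". At T3 and T4 there is a questionnaire only.

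**The concern.** Fidelity asks whether the provider delivered the intended content. The planned questions ask what the participant took away from it. These are different quantities, and here the second is reported under the name of the first.

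The second stated goal of the pilot is to prepare a full-scale randomized trial. The Limitations section concedes that one therapist delivers all the CBT, that reproducibility and scale-up are in doubt, and that effects of the intervention and of the interventionist may be hard to separate. A record of what that therapist covered is what would help with those doubts. The planned measure does not supply it, and following it as written could lead to a wrong conclusion on fidelity in either direction.

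**Working it through.** The plan gives no fidelity figure to reproduce, so the check sets the passages side by side and adds some date arithmetic.

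**1. What an answer can show.** For any one component there are four possible states and only two kinds of answer:

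| Component delivered? | Woman knows it at interview? | Answer | Read as fidelity | Correct? |
|---|---|---|---|---|
| Yes | Yes | Good | High | Yes |
| Yes | No (forgotten or not understood) | Poor | Low | No |
| No | Yes (learned elsewhere) | Good | High | No |
| No | No | Poor | Low | Yes |

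The interview alone cannot separate the first row from the third, or the second from the fourth. Learning elsewhere is plausible: all participants attend a mental health clinic, and the Design section describes referral to social work or psychiatry as needed. The article describes no comparison with what a woman already knew at T1.

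**2. What the tracked session data add.** The Design section plans eight sessions, so the tracked number gives sessions delivered out of 8. That is dose. No planned session length is stated, so tracked length has no standard to be compared with. Neither item says which of the five components was covered.

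**3. When the questions are asked.** The Feasibility section does not name the visit.
- T1 precedes CBT, and T3 and T4 have no interview, so on the stated schedule T2 is the only interview after CBT.
- The sessions are antenatal and so end by birth. The gap to T2 is therefore at least 2 months, about 2 × 4.35 = 8.7 weeks.
- Women enter at any gestational age, so the gap varies. Assuming birth at week 40, sessions ending at week 40 give (40 − 40) + 8.7 = 8.7, about 9 weeks. Sessions ending at week 16 give (40 − 16) + 8.7 = 32.7, about 33 weeks. Both end-weeks are assumptions, because the plan fixes neither session spacing nor gestation at entry.

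**4. What conflicts with that timing.** The Acceptability questions treat the baby as not yet born and labor as still ahead, although CBT has been received. They fit only an interview in pregnancy after CBT, and Data Collection schedules none. The Abstract also lists an intervention at two months postpartum where Data Collection has an interview. The 9 to 33 weeks therefore hold only if T2 is where the questions are asked.

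**5. Does the timing decide the point?** No. An interview in late pregnancy would shorten the delay, but the table in step 1 would still apply.

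**The case against.** The strongest case on the other side is that this is a pilot of 20 women with no fidelity threshold or decision rule. The five questions are offered as examples, a therapist's checklist often sits in a manual or full protocol, and the article already admits its dependence on one interventionist. A checklist ticked by that same therapist could simply be ticked throughout.

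Much of this stands as a limit on what can be claimed, and several stronger readings fail:

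- A reader might infer that the study can say nothing about delivery. It can: session number is tracked and can be set against the planned eight. Only adherence to content is unmeasured.
- A reader might take a recall delay of months as established. It is inferred from a schedule that conflicts with the acceptability questions.
- A reader might want to put a number on recall loss. The plan gives no recall rate, the five topics overlap, and each question names its topic. The plan also does not require a woman to answer on all five. Any such percentage would come from the assumptions put into it.
- A reader might assume that a therapist's session log already exists. The text says only that the sessions are tracked, not by whom or on what form.

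The objection does not remove the core. The article does not leave fidelity open: it states a method, and that method measures something else. The questions being examples does not help, because the stated source is still interviews with participants.

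**Conclusion.** The point holds in limited form. As the article describes it, fidelity is judged only from what women say they learned, which is receipt or comprehension. Dose can be recovered from the session tracking, but delivery of content cannot. The effect on the fidelity conclusion can go either way and cannot be sized from the document.

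The conclusion does not depend on when the interview takes place. If it is at T2, the delay is at least two months and varies with gestation at entry, which makes the answers harder still to read as delivery. The judgement rests on the method stated in the article; a treatment manual that is not shown could contain checks on the provider's side. The point is worth correcting because fidelity is a stated hypothesis and an input to the planned trial. It does not touch safety or the symptom outcomes.

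**What to change.** 1. When session number and length are tracked, also record at each session which of the five core components were covered.
2. Report fidelity as the proportion of the five components delivered per woman, alongside sessions delivered out of eight.
3. Keep the five interview questions and relabel them as receipt or comprehension.
4. Name the visit at which the fidelity and acceptability questions are asked, and reconcile Data Collection, Acceptability and the Abstract on this.

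The cost is small: at most 20 × 8 = 160 session records with five ticks each, summarised as 20 × 5 = 100 woman-by-component entries, and no additional staff. The form may have to be created, since the article does not describe one. The main weakness is that the therapist would probably complete it and may be optimistic, so it should be shown next to the women's accounts and disagreements between the two discussed.

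The cohort 2 abstraction item "care plan, including CBT interventions" could be applied to cohort 1 charts as a cross-check, but nothing in the article says that the care plan documents the five components. It should not replace the checklist unless that is confirmed.

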#### Acceptability

To assess acceptability of the intervention, we will ask four global open-ended questions assessing the perceived value of the intervention including:

What strategies do you see yourself using during labor/delivery and beyond?How has your CBT work impacted how you feel about labor/delivery and beyond?How has your CBT work impacted the way you feel towards your unborn child? Yourself? As a woman?Would you recommend this intervention to someone else in a similar situation as you? Why or why not?

### Statistical Analysis

For quantitative data, the overall impact of the PCNS-facilitated CBT intervention will be assessed using generalized estimating equations [41] to determine the effectiveness over time, and in contrast to standard care. Descriptive statistics, including measures of central tendency and dispersion, will be computed for all continuous variables and frequency tables will be constructed for all categorical variables.

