#### Maternal Attachment Inventory

Maternal-infant attachment will be evaluated using the MAI [39]. The MAI is a 26-item self-report instrument is measured on a four-point Likert scale, ranging from a) almost always, b) often, c) sometimes, and d) almost never. A total score is obtained by converting subjects’ responses to corresponding numeric values as follows: a) 4 points, b) 3 points, c) 2 points, and d) 1 point. All items are summed, resulting in scores ranging from 26 to 104. Higher scores indicate stronger feelings of attachment toward the newborn child. This instrument was initially tested in a sample of 196 women at one month postpartum, resulting in acceptable internal consistency and validity (alpha=.85) [39].

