### Power

#### Cohort 1

A sample of 20 women was selected as this is a feasibility study and it is anticipated we will reach saturation (assessed by the sole interviewer with the use of field notes) in the qualitative data [46]. This sample will be used to inform future power analysis for the large-scale RCT.

#### Cohort 2

One hundred charts will be audited (50 from each of the two arms, the intervention and standard care arms). This sample size, for this feasibility study, was selected as it will allow us to extend the breadth and depth of analysis from cohort 1. This ultimately enhances the validity of the study’s findings [31] by contextualizing the differences between the intervention and standard care, therefore contributing to valuable knowledge translation.

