### Limitations

The proposed study is not without limitations, namely the small sample size, limited recruiting methodology, and high reliance on the PCNS who is delivering CBT at the recruitment site. The small sample size chosen for this feasibility study is a limiting factor for statistical analyses as well. The fact that recruiting is limited to a single site could also be problematic as this significantly decreases the pool of potential participants. Finally, the high reliance on the PCNS who is delivering CBT at the recruitment site also limits the pool of participants, in addition to potential concerns regarding scale-up and reproducibility of the intervention. While having one intervention decreases the variability in terms of consistent delivery of the intervention, it speaks to a potential difficulty in ascertaining if the results were due to the intervention alone or the intervention/interventionist.

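### GEE for change over time rests on 20 women and needs a small-sample method: with default inference, a nominal 5% test would err about 7% (single contrast) to 12% (four-visit test)

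*Protocol article*

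**What the plan says.** The protocol article names one inferential method. Under Statistical Analysis, "the overall impact of the PCNS-facilitated CBT intervention will be assessed using generalized estimating equations", and the stated purpose is "to determine the effectiveness over time, and in contrast to standard care". The section adds descriptive statistics. It gives no variance estimator, working correlation, coding of time, named test or significance level.

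The other facts that bear on this point are:

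- **Number of women.** Under Power, "A sample of 20 women was selected as this is a feasibility study", together with an expectation of saturation in the interviews.
- **Visits.** Data Collection sets a baseline in pregnancy (T1) and then "two (T2), six (T3), and twelve (T4) months postpartum", so there are four occasions.
- **Cohort 2.** For the 100 charts, "the audit will be conducted for each chart in its entirety during a single data extraction period". The abstraction list names none of the questionnaire scales. Cohort 2 therefore adds nothing to the estimate of change over time on those scales.
- **Attachment.** For the Maternal Attachment Inventory (MAI), "Higher scores indicate stronger feelings of attachment toward the newborn child". T1 is antenatal, so this scale can probably be used only at T2 to T4. That is an inference; the article does not say it.
- **Acknowledged limit.** Under Limitations, "The small sample size chosen for this feasibility study is a limiting factor for statistical analyses as well". No remedy follows.

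**The concern.** Generalized estimating equations (GEE) are usually reported with the sandwich variance and normal or chi-square critical values. Both are justified when there are many independent units. Here the unit is the woman, and there are at most 20. At that size the sandwich variance is too small on average, and the large-sample critical values ignore the uncertainty in it. Intervals come out too short and p-values too small.

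A second feature of the method concerns losses. Unweighted GEE is consistent only if dropout is completely random, or depends only on covariates in the model. Follow-up runs to twelve months postpartum, and the Safety and Security section itself provides for women with whom contact is lost. A likelihood-based mixed model needs only that dropout depend on observed data, including earlier scores.

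At stake are the reported intervals and tests for the first four objectives (PTSD, depression, anxiety and attachment) and for the coping and quality-of-life scales. Readers will use them to judge whether the intervention looks promising enough for a full trial.

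**Working it through.** **No figure to reproduce.** The article gives no power calculation or significance level. The 20 is justified by feasibility and saturation.

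**Inputs from the article:** 20 women; four visits, so q = 3 degrees of freedom if visit is a factor; three visits for the MAI (inferred), so q = 2; a single contrast such as T1 to T2 has q = 1.

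**Assumed, because the article is silent:** two-sided 5% level; uncorrected sandwich variance; normal or chi-square critical values; normally distributed scores; n = 20 with complete data, or n = 15 if incomplete women are excluded.

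**Exact result for complete data.** With visit as a factor and everyone seen at every visit, the GEE estimates are the visit means. The sandwich covariance is then the sample covariance of the visit contrasts with divisor n instead of n − 1. The Wald statistic is W = T² × n/(n − 1), where T² is Hotelling's statistic. Since T²(n − q)/((n − 1)q) follows F(q, n − q), the true error is

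P{ F(q, n − q) > c × (n − q)/(nq) },

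where c is the 95% point of chi-square with q degrees of freedom.

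| q | c | F cut-off, n = 20 | True error, n = 20 | F cut-off, n = 15 | True error, n = 15 |
|---|---|---|---|---|---|
| 1 | 3.841 | 3.841 × 19/20 = 3.649 | 0.0713 | 3.841 × 14/15 = 3.585 | 0.0791 |
| 2 | 5.991 | 5.991 × 18/40 = 2.696 | 0.0946 | 5.991 × 13/30 = 2.596 | 0.1125 |
| 3 | 7.815 | 7.815 × 17/60 = 2.214 | 0.1237 | 7.815 × 12/45 = 2.084 | 0.1559 |

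**Interval width for one contrast.** The ratio of the default width to the correct t-based width is 1.960 × √((n − 1)/n) / t(0.975, n − 1).

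- n = 20: 1.910/2.093 = 0.913, about 9% too narrow; coverage 1 − 0.0713 = 92.9%.
- n = 15: 1.894/2.145 = 0.883, about 12% too narrow; coverage 1 − 0.0791 = 92.1%.

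At n = 20 the standard error alone is only 2.5% too small (√(19/20) = 0.975). The rest comes from using 1.960 in place of 2.093.

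**Check by simulation with losses.** Settings: 20 women, 10,000 runs each, no true change, compound-symmetry correlation 0.5 or AR(1) 0.6, 0 to 30% monotone random dropout, all available data used.

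- Uncorrected, four-visit overall test: 12.1% to 13.6%.
- Uncorrected, T4 versus T1 or linear trend: 6.9% to 7.5%.
- Uncorrected, three-visit overall test with complete data: 9.7%.
- Mancl-DeRouen variance with t or Hotelling-type F reference: 4.2% to 4.6% for a single contrast and 4.3% to 5.0% for the four-visit test.

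A separate simulation of 3,000 studies (correlation 0.6; 10, 20 and 30% lost at successive visits) gave 6.9% for T2 versus T1 and 13.5% for the four-visit test without correction. With a bias-reduced variance and t reference, T2 versus T1 gave 3.7%. The corrected tests are thus slightly conservative.

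**The case against.** The strongest objection is that the article says only GEE. It does not say that the variance will be left uncorrected, and it states no 5% test. A condensed article may leave the variance estimator and reference distribution to a full protocol or analysis plan, and GEE with a small-sample correction is sound. This stands to the extent that every error rate above is conditional on default settings. It does not remove the point: GEE is the one inferential method the article commits to, and whether it suits 20 women can be judged from the article itself.

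Three further objections also limit the point.

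- **Size.** A reader might infer that every test of change over time has a true error of 12% to 16%. The documents do not support that. The 12% belongs to an overall four-visit test that the article never names. About 16% requires that only 15 complete women are analysed; with all available data and up to 30% lost, the same test stays at 12.1% to 13.6%. Intervals go with single contrasts, where the error is about 7%.
- **Use in planning.** The Power section says that cohort 1 will inform the later power analysis. Standard deviations come from the descriptive statistics, and the choice of sandwich correction does not alter them. No p-value is said to decide whether the larger trial goes ahead.
- **Dropout.** A reader might infer that the estimates will be biased. The article gives no attrition figure, and the simulations measured error rates under random loss, not bias. The article also plans mitigation: an emergency procedure for lost contact, a safety plan reviewed throughout, and hardcopy completion in person where the electronic link is unsafe. What remains is that GEE rests on the stronger assumption.

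The Limitations section already concedes that the small sample constrains the analysis, but it changes nothing in the method.

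**Conclusion.** The point holds as a cheap improvement to a stated method; it does not invalidate the plan. Change over time rests on 20 women, and default GEE inference is anti-conservative at that size. The inflation is modest for a single contrast and clearer for tests over several visits. The sizes rest on the assumed two-sided 5% level, uncorrected sandwich, large-sample critical values and normal scores. If the full analysis plan already specifies a small-sample correction with t or F references, the error-rate part falls away and only the dropout assumption remains.

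**What to change.** For cohort 1, replace GEE in the Statistical Analysis section with a REML linear mixed model for repeated measures. Use visit as a factor, a within-woman covariance and Kenward-Roger degrees of freedom, and report changes with 95% confidence intervals. This uses every observed visit and is valid under missing at random. With complete data and an unstructured covariance, the T1 to T2 contrast becomes the paired t comparison, which holds its nominal level for normal scores.

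If GEE is kept, state that the Mancl-DeRouen or Fay-Graubard variance will be used with t and F reference values. This repairs the error rates but not the reliance on completely random dropout.

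The cost is one analysis sentence, standard software and slightly wider intervals: at n = 20 a single-contrast interval grows by a factor of about 1/0.913 = 1.10 with the t-based interval. An unstructured covariance over four visits has 4 × 5/2 = 10 parameters, so a simpler structure should be named in advance in case it does not converge.

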## Methods

### Design

This pilot project will consist of two cohorts: participants receiving CBT (cohort 1), as well as a retrospective chart audit of individuals who participated in the same CBT treatment within the last five years (cohort 2, intervention arm), and participants who received the accepted standard of care (cohort 2, standard care).

#### Cohort 1

A sample of 20 women currently attending the hospital-based, outpatient Perinatal Mental Health Clinic (London, Ontario, Canada) will be invited to participate in an eight-session antenatal CBT program facilitated by the clinic’s perinatal clinical nurse specialist (PCNS). CBT is currently the gold-standard approach for treating depression and anxiety. What is unique about this intervention is that it is tailored to the antenatal period and integrates attachment theory. Typically, women undergo initial screening at their pre-admission appointment for signs and symptoms of depression, anxiety, and PTSD, as well as for history of IPV. If women meet any of these criteria, they are referred for in-hospital social work or psychiatry consultations as necessary. While this intervention is currently provided to a small subset of women receiving antenatal care at the clinic, its efficacy remains untested. As such, this is considered a “specialty service” provided to identified at-risk women, and is not considered the accepted standard of care at this time.

#### Cohort 2

A retrospective medical chart review of 100 women will be conducted. All women must have received antenatal care at the recruiting hospital within the last five years and screened positive for IPV. This time frame was selected as it is representative of the duration in which the clinic’s current PCNS has been providing CBT to at-risk women. Of the 100 charts selected, 50 women must have participated in the CBT program (intervention arm), while the remaining 50 who did not will be assigned to the standard care group (these participants would have been eligible to participate but were not referred due to either lack of knowledge of the CBT program or a lack of support of the CBT program by the main health care provider). A sample size of 50 for both groups (intervention arm and standard care) will be sufficient to determine the feasibility of the study protocol for a future large-scale randomized control trial (RCT) [31].

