### Outcome Measures

All interviews and questionnaires seek to understand the lived experience of IPV within the context of pregnancy and childbirth, as well as the impact of CBT on the five primary study objectives described previously. Specifically, it is expected that this study will ascertain the impact of CBT on a) maternal mental health*,* and b) maternal-infant attachment. These outcomes will be measured using the PTSD Checklist (PCL-5), EPDS, Spielberger State-Trait Anxiety Inventory (STAI), World Health Organization Quality of Life Brief Assessment (WHOQOL-BREF), Maternal Attachment Inventory (MAI) and Proactive Coping Inventory (PCI). Each will be discussed in turn.

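### The plan promises a contrast with standard care over time, but describes no standard-care data on the six efficacy scales, so that contrast is not estimable

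*Protocol article*

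**What the plan says.** The Statistical Analysis section names one inferential method for all quantitative data. The overall impact of CBT "will be assessed using generalized estimating equations [41] to determine the effectiveness over time, and in contrast to standard care". It does not say which cohort or which outcomes feed which part of that sentence.

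The Outcome Measures section ties maternal mental health and attachment to self-report scales: "These outcomes will be measured using the PTSD Checklist (PCL-5), EPDS", then the STAI, WHOQOL-BREF, MAI and PCI. The Discussion (Study Rationale and Future Direction) defines efficacy by fewer symptoms and better attachment, coping and quality of life, which are the things these scales measure.

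A repeated schedule is given for cohort 1 only: "Data collection will occur at baseline (T1; prior to the PCNS-delivered CBT and during pregnancy), two (T2), six (T3), and twelve (T4) months postpartum". The Design section has all 20 of these women invited to CBT.

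Standard care enters only through cohort 2, where, of 100 charts, "the remaining 50 who did not will be assigned to the standard care group". For that cohort the Data Collection section states: "The chart review will take place at the recruiting hospital and does not require any patient contact". Its list of maternal items covers diagnosis and treatment, general health, obstetric history, birth, care plan, coping strategies, chart evidence of attachment, and demographics. Infant items are those recorded at birth. None of the six scales is on the list, and no repeated time points are set.

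**The concern.** The outcomes that define efficacy, the repeated visits and the standard-care group never occur together in any dataset the article describes. The scales and visits sit in a cohort with no comparator. The comparator sits in a cohort for which no scale is named. The analysis sentence nonetheless offers effectiveness both over time and against standard care, without limiting the second part to chart variables.

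An analyst following that sentence for the scales has two options: drop the promised contrast, or set prospective self-report scores against differently defined chart entries. The second would present uncontrolled change as if it were a controlled effect. This matters because efficacy is one of the two overarching goals, objectives 1 to 4 are to determine the impact of CBT, and the results are meant to inform a full-scale RCT. The Limitations section mentions sample size, the single site and reliance on one therapist. It does not mention that the scales have no control group.

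**Working it through.** The article gives no power calculation or effect size for this contrast, so there is no figure to reproduce. The check is whether the contrast can be estimated from the data described.

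**Inputs (Design, Data Collection, Outcome Measures, Power)**

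| | Cohort 1 | Cohort 2, CBT charts | Cohort 2, standard-care charts |
|---|---|---|---|
| Women | 20 | 50 | 50 |
| CBT | all invited | all | none |
| Six scales | planned | none named | none named |
| Defined repeated times | T1, T2, T3, T4 | none | none |

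**Model used for the check.** The article writes out no model. The simplest mean model that contains a contrast of two groups over four times is

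E(Y) = b0 + b1·G + Σ bk·Tk + Σ ck·G·Tk, for k = 2, 3, 4,

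with G = 1 for CBT. It has 1 + 1 + 3 + 3 = 8 parameters, one for each of the 2 × 4 = 8 group-by-time cells. A contrast is estimable only if it can be built from the means of filled cells.

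**Step 1: scale data as described.** There are 20 × 4 = 80 rows, all with G = 1. The G column then equals the intercept and each G·Tk column equals Tk, so the design has rank 4 of 8. Estimable: the CBT means and the within-CBT changes bk + ck. Not estimable: the group effect b1 and all three terms c2, c3, c4. The working correlation used in a GEE makes no difference to this.

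**Step 2: a generous assumption.** Suppose every cohort 2 chart yielded one scale score at one common time. One more cell is filled and the rank is 5 of 8. One between-group difference, at that time, becomes estimable. None of c2, c3 or c4 does, so a group difference in change still cannot be separated.

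**Step 3: what would be needed.** If standard-care women had each scale at all four times, the rank would be 8 of 8 and every contrast would be estimable. No such data are described.

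**Step 4: what cohort 2 can support.** For a chart variable taken once per woman, E(Y) = a0 + a1·G with 50 against 50 has rank 2 of 2. The difference between CBT and standard care is estimable, without a time dimension and not on the scales. For scale, assuming two-sided alpha 0.05 and complete data (neither is stated), the detectable standardised difference is (1.960 + z)·√(2/50) = (1.960 + z)·0.2. This is (1.960 + 0.842)·0.2 = 0.56 at 80% power and (1.960 + 1.282)·0.2 = 0.65 at 90%.

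**Step 5: can the gap be closed with data?** The Abstract (Results) says that cohort 2 data collection is finished. Data Collection says that no identifiers are kept and that each chart is audited in one go, so there is no route back to the same women's records.

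**The case against.** The strongest reply is that the sentence can be read as two aims: change over time in cohort 1, and CBT against standard care in cohort 2. Each can be fitted. With one observation per woman, a GEE reduces to a generalised linear model with robust standard errors. This stands, and it rules out several stronger readings that a reader might infer.

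- *That the GEE cannot be fitted at all.* It can, for change within cohort 1 and for a single-occasion chart comparison in cohort 2. Only the controlled comparison over time on the scales fails.
- *That the plan pools the cohorts, or that objectives 1 to 4 depend on a group-by-time term.* No pooled model or interaction is stated, and the objectives name no comparator. The eight-parameter model above is a device for checking estimability, not the plan's model.
- *That no standard-care woman has any score or repeated entry in her chart.* The text does not show this. The chart headings are broad, women are typically screened for depression, anxiety and PTSD, and a single extraction period describes when the chart is read, not how many dated entries it holds. What can be said is that no scale and no repeated time point is named for abstraction.

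It can also be argued that a short article leaves such matters to an SAP, and that this is only a pilot. An SAP can assign outcomes to models and add covariates. It cannot supply a comparator that the described data collection does not gather. The two-aim reading is also not what the text says: it speaks of one overall impact and does not confine the standard-care contrast to chart variables.

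**Conclusion.** The sentence is wrong as written for the outcomes that define efficacy. For all six scales, none of the four standard-care cells is described as collected, and none of the group or group-by-time contrasts is estimable. Even one score per chart would not yield a difference in change. Two things remain available: uncontrolled change in cohort 1, and an observational comparison of chart variables in cohort 2.

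This rests on reading the abstraction list as it stands, with no scale and no defined repeated times. If the abstraction instrument did capture dated scale scores for standard-care women, the article would need to say so and the conclusion would have to be revisited. The point should be corrected before analysis, because otherwise uncontrolled change could be reported as a controlled effect.

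**What to change.** Replace the sentence with two separate, unpooled analyses.

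1. **Cohort 1.** GEE for within-woman change on each scale from T1 to the later visits, labelled uncontrolled. State explicitly that the scales are given at T1: Data Collection names only an interview and a demographic survey for T1 and T2, and the Abstract mentions questionnaires only from two months postpartum. Describe and compare the MAI only from T2 onward, because it concerns the newborn and T1 falls in pregnancy.
2. **Cohort 2.** CBT against standard care on the abstracted maternal and infant chart outcomes, by adjusted linear or logistic regression (or a single-occasion GEE). Label it observational, since the arms differ by referral and not by randomisation, and make no claim about change over time. Maternal items need not be limited to birth, as only the infant items are tied to it.

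Confine the contrast with standard care to the cohort 2 chart outcomes. Reword objectives 1 to 3 as estimating uncontrolled change in cohort 1. Reword objective 4 as describing postpartum MAI scores in cohort 1 and comparing chart evidence of attachment in cohort 2.

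The cost is wording, with no new data provided that the scales are indeed given at T1. The downside is that the stated efficacy aim becomes more modest.
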